# Spinal manipulation and exercise for low back pain in adolescents: study protocol for a randomized controlled trial

**DOI:** 10.1186/2045-709X-22-21

**Published:** 2014-05-23

**Keywords:** Back pain, Pain, Spinal manipulation, Musculoskeletal manipulations, Exercise, Randomized controlled trial, Adolescent

## Abstract

**Background:**

Low back pain is among the most common and costly chronic health care conditions. Recent research has highlighted the common occurrence of non-specific low back pain in adolescents, with prevalence estimates similar to adults. While multiple clinical trials have examined the effectiveness of commonly used therapies for the management of low back pain in adults, few trials have addressed the condition in adolescents. The purpose of this paper is to describe the methodology of a randomized clinical trial examining the effectiveness of exercise with and without spinal manipulative therapy for chronic or recurrent low back pain in adolescents.

**Methods/design:**

This study is a randomized controlled trial comparing twelve weeks of exercise therapy combined with spinal manipulation to exercise therapy alone. Beginning in March 2010, a total of 184 participants, ages 12 to 18, with chronic or recurrent low back pain are enrolled across two sites. The primary outcome is self-reported low back pain intensity. Other outcomes include disability, quality of life, improvement, satisfaction, activity level, low back strength, endurance, and motion. Qualitative interviews are conducted to evaluate participants’ perceptions of treatment.

**Discussion:**

This is the first randomized clinical trial assessing the effectiveness of combining spinal manipulative therapy with exercise for adolescents with low back pain. The results of this study will provide important evidence on the role of these conservative treatments for the management of low back pain in adolescents.

**Trial registration:**

(ClinicalTrials.gov NCT01096628).

## Background

### Low back pain prevalence and burden in adolescents

Low back pain (LBP) in adolescents has become increasingly recognized as a public health concern, with an estimated one year prevalence of 34% [1]. Often beginning at a young age, the prevalence of LBP quickly mirrors that of adults by the late teenage years [2]. The natural history of LBP in adolescents is also similar to adults with recurrent symptoms occurring in over one half of patients [3]. Importantly, recurrent LBP in adolescence is highly associated with continued pain in adulthood [4,5].

While the prevalence of LBP steadily increases with age during childhood, the number of adolescents seeking care does not dramatically increase until mid-adolescence [6]. Care-seeking for LBP in childhood is strongly influenced by pain intensity and limitations in daily activities [7]. Approximately one-quarter of adolescents with LBP miss school because of their LBP condition [8].

Although little is currently known regarding the societal cost of LBP in adolescents, the disease burden in adulthood is substantial. The 2010 Global Burden of Disease study ranked LBP as the leading cause of years lived with disability in the world [9]. After respiratory disorders, LBP causes more short-term work absence that any other condition [10]. In the US alone, costs associated with LBP are estimated between $20 and $120 billion annually and are increasing [11,12]. In addition, there are growing concerns regarding the overutilization and safety of frequently prescribed medical treatments, particularly in light of the lack of evidence to support their effectiveness [13].

Recognizing that LBP begins at an early age and becomes burdensome and costly in adulthood, research focusing on conservative management strategies for adolescents with LBP is urgently needed.

### Treatment of adolescent LBP

Whereas multiple randomized trials have examined the effectiveness of commonly used conservative treatments for LBP in adults [14-17], few have been performed in adolescent LBP populations. Three small randomized clinical trials have evaluated exercise as a treatment approach for adolescent LBP [18-20]. Collectively, the published trials to date suggest exercise may be effective in reducing pain and disability in adolescents with LBP, but larger, high quality trials are needed. Interestingly, although spinal manipulative therapy (SMT) is commonly used for children with spine conditions [21], no randomized trials examining the effectiveness of SMT for adolescent LBP have been published to date [22].

### Study aims

Our primary aim is to determine the relative clinical effectiveness of 1) exercise with SMT versus 2) exercise alone in 184 adolescents with sub-acute recurrent (2-12 weeks) or chronic (>12 weeks) LBP, measured at 12, 26, and 52 weeks. The primary outcome measure is patient-rated LBP at these time points. Our hypothesis is that the addition of SMT to exercise will reduce pain more than exercise alone.

Our secondary aims are to assess between-group differences in disability, quality of life, improvement, satisfaction, activity level, dynamic lumbar motion, and trunk muscle endurance. In addition, we will assess the participant’s perceptions of treatment using qualitative interviews.

## Methods/design

### Design & setting

This trial began in March 2010, and is a two-site, parallel-group randomized controlled trial. Participants are being recruited at Northwestern Health Sciences University in Bloomington, MN and the University of Western States in Portland, OR. All treatments are provided within university-associated outpatient clinics.

### Ethical approval

Ethical approval has been granted by the Institutional Review Boards of the participating institutions (Project ID: 1-77-10-09).

### Recruitment

Potential subjects are recruited from the Minneapolis/St. Paul, MN and Portland, OR metropolitan areas using multiple methods. The primary recruitment method is targeted mailings to households with adolescents. Other recruitment methods include internet advertising through Facebook and Craigslist, newspaper advertising, flyers, and targeted referral letters to local physicians specializing in pediatrics or musculoskeletal conditions and coaches of sport programs at local schools.

### Participants

Adolescents, age 12 to18, with a history of sub-acute recurrent or chronic low back pain are eligible to participate. The inclusion/exclusion criteria are described in Table 1.

**Table 1 T1:** Inclusion and exclusion criteria

**Inclusion criteria**	**Exclusion criteria**
• 12 to 18 years old	• Spinal manipulative therapy or exercise therapy in the previous month
• Either:	
◦ Sub-acute recurrent non-specific low back pain defined as current episode of 2 to 12 weeks duration AND an additional 2 week episode of back pain in the past year	• Ongoing treatment for low back pain by other health care providers
	• Other serious physical or mental health conditions (e.g., uncontrolled diabetes, cancer)
OR	• Contraindications to study treatments including acute disc herniation, clinical
◦ Chronic non-specific low back pain defined as a current episode ≥ 12 weeks duration	
	• instability of the lumbar spine, or inflammatory arthritides
• Low back pain intensity ≥ 3 on 0 to 10 numerical rating scale	• Benign joint hypermobility syndrome
• Stable prescription medication plan (no changes to prescription medications that affect musculoskeletal pain in the previous month)	

### Baseline assessments

Interested individuals are assessed for eligibility and compliance during a scripted telephone interview followed by three distinct baseline evaluations. For participants ages 12-17, written assent is obtained in addition to written informed consent from a legal guardian. Participants 18 years of age provide written informed consent. Individuals complete a clinical health history and physical exam. Plain film radiographs are taken if suspicion of a specific cause of LBP is present. To maintain consistency across sites, study clinicians and investigators, who are blinded to upcoming treatment assignment, meet (in-person and by teleconference) to review each case to determine eligibility. Self-report outcome measures and blinded objective assessments of lumbar spine motion, strength, and endurance are completed at the first two baseline evaluations. An accelerometer is issued to potential participants to monitor their physical activity level for the week prior to treatment assignment. Participants are assigned to study treatments at the third baseline evaluation. The participant’s flow through baseline evaluations and treatment is shown in Figure 1.

**Figure 1 F1:**
[figure not shown]
**Study flow diagram. Self-report Outcomes:** Primary and secondary outcomes (e.g., Pain, Disability). **Objective Biomechanical Outcomes:** Torso muscle strength & endurance; Continuous lumbar motion; Accelerometer readings for 7 consecutive days. **Qualitative Interview:** Face-to-face interviews assessing treatment experience and expectations.

### Treatment allocation & concealment

As participants become eligible, study staff masked to upcoming treatment assignments use a dynamic allocation (rank-order minimization) computer program to assign subjects to treatment [23-25]. Gender, age, pain duration, and intensity are entered into the program to balance patient characteristics between groups.

A computer-generated random allocation sequence secured in sealed, opaque, sequentially numbered envelopes is used to randomize the first six participants at each site to provide a “seed” group of participants for the dynamic allocation program. Envelopes are also used as a back-up in the event the treatment allocation program becomes unavailable.

### Interventions

All interventions are provided by study staff at Northwestern Health Sciences University and the University of Western States research clinics. The physical nature of the treatments prevents blinding of participants and providers to treatment assignment. Participants are asked not to receive care for their LBP condition from other providers during the active treatment phase (12 weeks). Data regarding non-study care is collected in the self-report questionnaires.

Treatment providers have been trained in protocols to ensure standardized intervention and documentation. To facilitate protocol adherence, clinical records are monitored weekly by research staff. Non-adherent providers and patients are contacted using various methods (e.g., in-person, by phone, or email) to resolve compliance issues.

#### Exercise therapy (ET)

There are three components to the ET program: self-care education, supervised exercise visits, and home exercise. The overall objectives are to help adolescents manage their LBP and prevent future LBP recurrences. The total number of visits ranges from 8 to 16, depending on the patient’s needs (e.g., ability to perform exercises independently). Experienced chiropractors and exercise therapists have been trained and certified to deliver the program.

The details of the exercise program are outlined in Table 2. Each visit starts with 10 minutes of self-care education to help patients establish and monitor goals aligned with the exercise program and enhance their understanding of LBP. Participants are taught the importance of movement and activity, pain management techniques, and methods for developing spinal posture awareness during activities of daily living (e.g., lifting, pushing, pulling, sitting, getting out of bed, and using a backpack). Individuals are provided printed instructions and photos of exercises in addition to a modified *Back in Action*[26] binder, which emphasizes movement and restoration of normal function and fitness [27,28]. The supervised exercises begin with a 5-minute, light aerobic ◦warm up, followed by stretching and strengthening exercises (bridge, abdominal crunches, quadruped, side bridge, and back extensions). Participants begin with exercises appropriate for their fitness level and gradually progress in difficulty by changing body position and/or using a labile surface (i.e., gym ball). Participants are encouraged to perform the same exercises at home combined with 20-40 minutes of aerobic activity two times per week.

**Table 2 T2:** Treatment interventions

**Intervention**	**Spinal Manipulative Therapy (SMT)**	**Exercise Therapy (ET)**
**Type**	• High velocity, low amplitude SMT preferred	**ET Visit**
		Self-care education
	• Other manual therapies if needed	• Supervised exercise
	◦ Low velocity, low amplitude SMT or mobilization	
		◦ Aerobic warm up
	◦ Flexion-distraction manipulation	
	◦ Drop-table assisted SMT	◦ Stretching (cat/camel, piriformis, hamstring, laying back rotation)
	• Up to 5 minutes adjunct therapies to facilitate SMT:	
	◦ Light soft tissue massage, active and passive stretching, ischemic compression of tender points, ice and heat	◦ Strengthening (bridge, abdominal curl, back extension, side bridge, quadruped, and squats) with changes in body positioning and addition of labile surface (i.e., gym ball) for progressions
		**Home Exercise**
		• Instructions provided at treatment visits and supplemented by take home materials
**Design & delivery format**	• Individualized: number of visits, spinal levels treated, SMT and manual therapy technique used and adjunct therapies determined by provider according to patient needs and tolerance	**ET Visit**
		• Supervised
		• Individualized: number of visits, exercise progressions determined by provider
		**Home Exercise**
		• Unsupervised
**Delivery method**	• One-on-one treatment visit	**ET Visit**
	• Treatment provided by licensed chiropractor	• One-on-one exercise therapy visit
		• Instructions and supervision provided by licensed chiropractor or exercise therapist
		**Home Exercise**
		• Instructions provided at treatment visits
		• Instructions supplemented by take home materials (exercise photos, modified *Back in Action*[26] book)
**Dose**	• 8 to 16 treatment visits	**ET Visit**
	• 10 to 20 minutes per visit	• 8 to 16 visits
	• Maximum frequency: 2 times/week	
		• 45 minutes per visit
		◦ 10 minutes self-care education
		◦ 5 minutes aerobic exercise warm up
		◦ 30 minutes supervised exercise
		▪ Stretching: 1 set; 3 reps
		▪ cat/camel; 1 rep each side for other stretches
		▪ Strengthening: 2 sets; 16 to 20 repetitions each exercise
		**Home Exercise**
		• Maximum frequency: 2 times/week

#### Exercise therapy combined with spinal manipulative therapy (ET + SMT)

Participants in the ET + SMT group participate in the same ET program described above. In addition, they take part in 8 to 16, 10- to 20-minute sessions of SMT over 12 weeks (Table 2). Previous research has shown that 9 to 12 treatments are more beneficial than 3 to 6 treatments for adults with LBP [29]. The number and frequency of treatments is determined by the individual chiropractor based on patient-rated symptoms and exam findings [30]. SMT is provided by experienced chiropractors following standardized treatment protocols. The preferred treatment consists of a high-velocity, low amplitude thrust SMT. The treating chiropractor has the option to perform other techniques (e.g., flexion-distraction, spinal mobilization, or neuromuscular techniques) [31], as indicated. Light soft tissue techniques (i.e., active and passive muscle stretching, hot and cold packs, and ischemic compression of tender points) may be used as needed to facilitate the manual therapy.

#### Modification and discontinuation of treatment

Prescription-strength nonsteroidal anti-inflammatory rescue medications are available for patients experiencing severe pain and are prescribed as needed by a study medical doctor. Any patient who demonstrates progressive neurological signs or severe intractable pain is removed from study treatment and referred for orthopedic consultation. Participants who receive medications or are discontinued from treatment will be included in the intention-to-treat analyses.

### Outcomes

Patient self-report outcomes are collected at the first two baseline visits and at 4, 8, 12, 26, and 52 weeks after randomization. The self-report outcomes are based on the Pediatric Initiative on Methods, Measurement, and Pain Assessment in Clinical Trials (PedIMMPACT) groups’ recommendations [32]. Objective spinal biomechanical outcome measures are collected at the first two baseline visits and at 12 and 26 weeks after study enrollment by examiners blinded to treatment assignment. The participant’s physical activity level is assessed at baseline and at weeks 12 and 26. Qualitative interviews are conducted at 12 weeks (end of treatment) to ascertain their perceptions of treatment.

#### Primary outcome

##### Pain

Patient-rated low back pain at 12, 26, and 52 weeks, measured by the 11-box numerical rating scale, is the primary outcome measure. LBP at 4 and 8 weeks is a secondary outcome. Pain severity is regarded as one of the most important clinical outcomes by adults with spinal pain [33,34] and is recommended as a core outcome by an international group of back pain researchers in addition to the PedIMMPACT group [32,35]. The 11-box numerical rating scale for pain has been shown to perform similarly to the visual analogue scale (VAS) in both pediatric and adult populations [36,37].

#### Secondary outcomes

##### Disability

Patient-rated disability is assessed using the 18-item Roland-Morris Disability Questionnaire. The 18-item Roland-Morris Disability Questionnaire has been shown to be reliable, valid, and as responsive as the original 24-item Roland-Morris Disability Questionnaire [38,39].

##### Quality of life

Participants rate their quality of life using the 23-item PedsQL instrument, which has been developed to measure physical, emotional, social, and school functioning domains in children 8 to 18 years old. The PedsQL is a reliable, valid, and responsive measure of quality of life [40-43].

##### Improvement

Patient-rated improvement is determined by asking participants to compare their LBP condition to what it was before study treatment on a 9-point scale ranging from no symptoms (100% improvement) to as bad as it could be (100% worse). The caregiver’s impression of improvement will also be measured using the same 9-point scale. Improvement is an important outcome that has shown to be responsive [44].

##### Satisfaction

The participant’s overall satisfaction with care is assessed with a 7-point scale ranging from completely satisfied (couldn’t be better) to completely dissatisfied (couldn’t be worse). The caregiver’s satisfaction with care is also evaluated using the same scale. Research examining global satisfaction with treatment in pediatric pain trials is lacking and has been identified as an area of great need by the PedIMMPACT group [32].

##### Adverse events

The complete reporting of adverse events in clinical trials has received little attention [45]. To address this, we collect adverse event information at several levels. First, participants are queried about expected adverse events in the self-report questionnaires by choosing from a list generated from previous studies [46,47]. Participants are asked to rate the bothersomeness of each adverse event on a 0 to10 scale (0 = not at all bothersome, 10 = extremely bothersome). In addition, they are asked about new or ongoing adverse events at each treatment visit; these are recorded on standardized treatment notes. Finally, all patients are instructed to a report serious adverse event at any time to study staff (see Data and Safety Monitoring below).

##### Expectation

Participants rate their perception of how helpful they believe each treatment will be on a 1 to 5 scale (1 = Much better, 5 = Much worse) prior to randomization. After randomization, participants are asked to estimate the degree of improvement they expect to have after 12 weeks of care using the 9-point improvement scale described above.

##### Health care utilization and compliance

Patients report the number of visits and care received from non-study health care providers. They also report the number of days they took medication for LBP and performed the study exercises in the past week.

#### Qualitative outcomes

##### Qualitative interviews

One-on-one interviews are conducted at 12 weeks. A schedule of questions is used to direct the interviews and keep the interviewers on a path consistent with the purpose of the study [48]. The questions begin broadly, asking how patients felt about the treatment they received, whether it met their expectations, and what they liked and disliked. These questions are followed by probe questions to elicit underlying reasons.

#### Objective biomechanical outcomes

##### Continuous lumbar motion

Lumbar spinal motion is assessed using the Zebris CMS-HS Spine Motion Analyzer (Zebris Inc., Isny im Allgau, Germany), a reliable and accurate measurement system [49,50]. Lumbar flexion-extension, rotation, and side-bending are examined using a modified protocol described by Vogt et al [51].

##### Torso muscle strength & endurance

Endurance of the lower back musculature (trunk flexors, lateral flexors, and extensors) is examined using the protocol described by McGill [52]. The tests have been shown to be a valid and reliable measure of torso muscle endurance [53,54]. Maximum isometric strength of trunk flexors and extensors is measured using a modified standing method described by Jørgensen and Nicolaisen [55,56].

##### Activity level

Participants’ physical activity level is assessed by having them wear a GT3X accelerometer (Actigraph, Inc. Pensacola, FL) for 7 consecutive days prior to randomization, then again prior to the week 12 and 26 evaluations. The GT3X accelerometer has been found to be a reliable and valid measure of physical activity level [57].

### Analysis plan

For the primary analysis, patient-rated low back pain will be analyzed at 12, 26, and 52 weeks with linear mixed model regression to estimate mean differences between treatment groups at each time point adjusting for baseline covariates (i.e., rank-order minimization variables) and accounting for correlation across measurements within person. Short- and long-term longitudinal effects between groups will also be assessed using mixed model analyses including LBP intensity outcomes from weeks 4 to 12 and weeks 4 to 52, respectively. Due to the longitudinal study design, the primary analysis plan was modified from a one-way analysis of covariance to a linear mixed model approach to allow increased flexibility when specifying a variance-covariance structure and accounting for missing data [58-60]. The analysis plan was modified prior to the completion of data collection and the start of data analysis.

The variance-covariance structure that best fits the data will be used to account for correlation among the repeated measurements within participants [61,62]. Normality assumptions will be evaluated through normal probability plots and transformations used, if necessary. We will test for a site-by-group interaction, but given our standardization plan, we do not expect it to be present. Adjusted mean differences and 95% confidence intervals between groups for short- and long-term effects based on the final models will be presented in tables and line graphs. The need for inclusion of additional covariates to balance baseline group differences will be evaluated in sensitivity analysis. Intention-to-treat analysis will be used; all patients with at least one follow-up measure will be included in the analysis as the methods do not require data at every time point. In the event that missing data is present, the pattern of missingness will be assessed and appropriate imputation and sensitivity analyses will be performed. Responder analyses (i.e., 50, 75, and 100% pain reduction) will be conducted to facilitate the interpretation of the results [63-65].

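### As worded, the primary mixed model takes only weeks 12, 26 and 52 as responses, so a participant seen only at week 4 or 8 contributes nothing to the primary estimate, contrary to the plan's own inclusion rule

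*Protocol article*

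**What the plan says.** The primary outcome is defined under Pain: "Patient-rated low back pain at 12, 26, and 52 weeks, measured by the 11-box numerical rating scale, is the primary outcome measure". The same paragraph adds that "LBP at 4 and 8 weeks is a secondary outcome".

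Under Outcomes, all five follow-up visits are scheduled: "Patient self-report outcomes are collected at the first two baseline visits and at 4, 8, 12, 26, and 52 weeks after randomization".

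The Analysis plan states that, for the primary analysis, "patient-rated low back pain will be analyzed at 12, 26, and 52 weeks with linear mixed model regression". Short- and long-term effects are then introduced as something also to be assessed, through "mixed model analyses including LBP intensity outcomes from weeks 4 to 12 and weeks 4 to 52, respectively". The section explains the move from analysis of covariance to a mixed model partly by the wish to deal with missing data.

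On who is analysed, it says that "all patients with at least one follow-up measure will be included in the analysis as the methods do not require data at every time point". On incomplete data, it says that "the pattern of missingness will be assessed and appropriate imputation and sensitivity analyses will be performed".

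**The concern.** A likelihood-based mixed model uses incomplete participants only through the outcomes that are in its response vector. With weeks 12, 26 and 52 as the only responses, someone last seen at week 4 or 8 has no row in the model. Yet a week-8 score is plainly a follow-up measure on the plan's own schedule, and the inclusion rule justifies itself by saying that the method tolerates missing visits. The rule and the model as worded do not fit together.

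It also weakens the missing-at-random assumption. If leaving between weeks 8 and 12 depends on pain at week 8, the loss is random given the week-8 score, but not given what a 12/26/52 model contains. Participants know their treatment (Interventions), so a different dropout pattern in each arm is conceivable. At stake are a possible bias in the primary difference and a small loss of precision, both avoidable with data that are collected anyway.

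**Working it through.** **Inputs from the Protocol article (Power analysis and sample size).** SD of change 1.4, R² 0.2, target difference 0.8, alpha 0.01, power 0.92, 80 per group, loss of up to 15%, 92 per group enrolled.

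**The plan's own figure.** Adjusted SD = 1.4 × √(1 − 0.2) = 1.252, variance 1.568. With two-sided alpha 0.01, n = 2 × (2.576 + 1.405)² × 1.568 / 0.8² ≈ 78 per group by the normal approximation. At 80 per group the noncentral t gives power 0.9225. The stated 80 and 0.92 are reproduced, so 1.252 is a fair residual SD for what follows.

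**Assumptions not in the documents.** Correlation between visits 0.3 to 0.7 for precision and 0.5 to 0.7 for bias. Share lost between weeks 8 and 12: 5% (about 5 of 92 per arm), or the whole 15% allowance (about 14 of 92).

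**Precision at week 12.** With the 12/26/52 model and all 14 lost in that window, 78 per arm remain:
- SE = 1.252 × √(2/78) = 0.2005.

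If week 8 is in the model and correlation decays with visit spacing, the variance becomes 2 × 1.568 × [(1 − ρ²)/78 + ρ²/92]:
- ρ = 0.3: SE 0.1991.
- ρ = 0.7: SE 0.1929.

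With equal correlation between all visits, week 4 helps too, and at ρ = 0.7 the SE is 0.1915. The 12/26/52 SE is thus 0.7% (0.2005/0.1991) to 4.7% (0.2005/0.1915) larger. With 5 per arm lost in the window, 0.1899 compares with 0.1894 to 0.1869, a loss of 0.2 to 1.6%. With 78 per arm the planned power is still about 0.915.

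**Bias at week 12.** Let z be standardised week-8 pain, with the log-odds of loss rising by 0.7 or 1.0 per SD. In an arm where loss depends on pain, the mean week-12 score of those retained shifts by ρ × 1.252 × E(z | retained).

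| Lost, weeks 8–12 | Log-odds per SD | E(z given retained) | Shift, ρ = 0.5 | Shift, ρ = 0.7 |
|---|---|---|---|---|
| 5% | 0.7 | −0.034 | −0.02 | −0.03 |
| 5% | 1.0 | −0.047 | −0.03 | −0.04 |
| 15% | 0.7 | −0.099 | −0.06 | −0.09 |
| 15% | 1.0 | −0.133 | −0.08 | −0.12 |

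- Dependence in one arm only: the group difference is off by the tabled shift, 0.02 to 0.04 points with 5% lost and 0.06 to 0.12 with 15%.
- Opposite dependence in the two arms: the shift doubles, to 0.04 to 0.08 with 5% and 0.12 to 0.23 with 15%.
- Same dependence in both arms: the shifts cancel and there is no bias.

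Where the bias attenuates, a true difference of 0.80 is estimated as 0.76 to 0.78 (one arm) or 0.72 to 0.76 (opposite) with 5% lost. With 15% lost it is 0.68 to 0.74 or 0.57 to 0.68. Swapping the arms reverses the sign. In simulation under this mechanism, including the early visits returns 0.80.

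**The case against.** The strongest reply is that exclusion is inferred, not stated. Naming the three weeks could describe the contrasts to be reported and not the response vector, and the inclusion rule could be read as already admitting a week 4 or 8 score. Restricting the primary model to the declared primary time points is also a legitimate choice that matches the outcome definition. Further, imputation is promised and could draw on weeks 4 and 8, and a condensed article may leave its details to a fuller document.

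Part of this stands. The text can be read more generously, so a clarification may be all that is needed. But the weeks 4–12 and 4–52 models are introduced as additional to the primary analysis, which makes the narrow reading the plain one. On that reading two statements in the same section collide, which is not a matter of omitted detail. The promised imputation is conditional and unspecified, and does not define the primary estimate.

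A reader might also infer three stronger things that the documents do not support:
- That week 4 and 8 pain is ignored. It is a declared secondary outcome and enters two planned models.
- That everyone lost after week 8 leaves the primary analysis. Someone lost after week 12 or 26 still contributes; only those with no score at 12, 26 and 52 fall out.
- That choosing the best-fitting covariance structure is part of this fault. It is a separate question, and any figure for it needs a selection rule that the article does not name.

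**Conclusion.** The point holds as an internal inconsistency with a nearly free remedy. On its plain wording, the primary model omits participants whom the plan's own rule includes, and it omits the two visits closest to any loss between weeks 8 and 12.

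The size is modest. The week-12 standard error is about 0.2 to 5% larger than it need be, which does not threaten power. The figures of 0.12 to 0.23 points should not be read as the expected bias. They require the whole 15% allowance to fall in one four-week window, although follow-up runs to week 52, and they require opposite dropout mechanisms in the two arms, for which the document offers no evidence. With 5% lost in that window, the bias is 0.02 to 0.08 points, against a standard error of about 0.19 and a target of 0.8. All bias figures rest on the assumed log-odds and correlations. Full recovery by adding weeks 4 and 8 holds only if dropout is missing at random given those scores. The change is worth making, but the trial is not invalid without it.

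**What to change.** Fit the primary mixed model to all five follow-up visits (4, 8, 12, 26 and 52) with group-by-visit terms, and keep the group differences at 12, 26 and 52 weeks as the primary contrasts. State that a score at any of these five visits counts as a follow-up measure for inclusion. The primary outcome does not change, and week 4 and 8 pain stays secondary.

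The cost is wording. The data are already collected and a weeks 4–52 model is already planned. An unstructured covariance matrix grows from 3 × 4 / 2 = 6 to 5 × 6 / 2 = 15 parameters, which about 160 participants can support. Name a simpler structure in advance as the fallback for non-convergence.

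### The primary mixed model adjusts for the four minimisation variables but not for site; adding site is a small, free improvement

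*Protocol article*

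**What the plan says.** Under Design & setting, the protocol article states that the study "is a two-site, parallel-group randomized controlled trial". Under Treatment allocation & concealment, masked staff "use a dynamic allocation (rank-order minimization) computer program to assign subjects to treatment". The inputs are listed: "Gender, age, pain duration, and intensity are entered into the program to balance patient characteristics between groups". Site is not one of them. Site enters allocation explicitly only at the start, where an envelope sequence "is used to randomize the first six participants at each site", giving the program its seed group. The section does not state whether the program then works separately at each site or on both sites together.

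Under Analysis plan, the primary linear mixed model estimates group differences at 12, 26 and 52 weeks, "adjusting for baseline covariates (i.e., rank-order minimization variables"). Site is mentioned once in that section: "We will test for a site-by-group interaction, but given our standardization plan, we do not expect it to be present". Further covariates that might be needed because of baseline differences are assigned to sensitivity analysis.

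**The concern.** The abbreviation i.e. defines the covariate set rather than illustrating it. The article therefore makes a choice here; it does not leave the matter open for a fuller document. On that choice, the model behind the headline estimate has no term for site.

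Site could plausibly relate to pain at follow-up. The two sites recruit from different metropolitan areas and treat in different clinics. The standardisation plan is offered as a reason not to expect the treatment effect to differ between sites. It does not address whether average pain differs between sites.

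There are two possible consequences, and they are alternatives:

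- If arms are balanced within site, between-site variation stays in the error term. The standard error is then larger than it need be and the test is conservative.
- If balance by site is left to chance, a site imbalance between arms carries through to the primary estimate without correction.

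**Working it through.** **Inputs from the article (Power analysis and sample size).** Difference 0.8 points; SD 1.4; R² 0.2; alpha 0.01; power 0.92; 80 evaluable per group; 92 per group and 184 in total after the dropout allowance.

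**Assumptions not in the article.** Between-site difference in mean follow-up pain, d: 0.4 to 0.6 points, with wider values shown below. Sites of equal size. For a given d, equal sites give the largest effect, because the between-site variance is p(1−p)d², which peaks at p = 0.5, where it equals (d/2)².

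**Step 1. Reproduce the plan's figure.** Residual SD = 1.4 × √(1 − 0.2) = 1.252. Two-sided normal approximation: n = 2 × (2.576 + 1.405)² × 1.252² / 0.8² ≈ 78 per group. A noncentral-F calculation for ANCOVA with 80 per group gives power 0.922. The stated 80 per group and 0.92 reproduce, so 1.252 is a fair working SD.

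**Step 2. Arms balanced within site: precision.** Take 1.252 as the SD before site is removed. Share of variance due to site = (d/2)² / 1.252².

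| d | Share due to site | SE ratio √(1 − share) | SE narrows by | Equivalent participants, 160/(1 − share) − 160 |
|---|---|---|---|---|
| 0.4 | 0.04/1.568 = 2.6% | 0.987 | 1.3% | about 4 |
| 0.6 | 0.09/1.568 = 5.7% | 0.971 | 2.9% | about 10 |

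**Step 3. Arms balanced within site: error rate and power.** Here 1.252 is taken as the within-site SD, so the model without site uses √(1.252² + d²/4). This differs slightly from the convention in step 2, but the two agree closely at these values of d. Normal approximation, 80 per group, nominal two-sided alpha 0.01. With site in the model, power is 0.929.

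| d | Actual alpha, site omitted | Power, site omitted |
|---|---|---|
| 0.25 | 0.0096 | 0.927 |
| 0.5 | 0.0086 | 0.921 |
| 1.0 | 0.0055 | 0.897 |
| 1.5 | 0.0027 | 0.850 |

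The loss is 0.929 − 0.921 = 0.008 at d = 0.5, about 3 percentage points at 1.0 and about 8 at 1.5. Type I error falls below nominal; it is not inflated.

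**Step 4. Site balance left to chance.** If 55% of one arm and 45% of the other come from the same site, the unadjusted difference shifts by (0.55 − 0.45) × d = 0.04 to 0.06 points. With equal-sized sites and 80 to 92 per arm, the SD of the gap in site mix is √(2 × 0.25/n) = 0.079 to 0.074. A gap of at least 0.10 in either direction then arises by chance in roughly 17 to 21% of trials. The SE of the group difference is 1.252 × √(2/80) = 0.198, so a shift of 0.06 is about 0.3 of a standard error.

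**The case against.** The strongest reply is that the plan is consistent with itself. It adjusts for exactly the variables listed as inputs to the minimisation, so the allocation and analysis sections agree. The loss is also small: under 1 percentage point of power at a site difference of 0.5, and a material loss only if the sites differ by more than the treatment effect being sought. Providers are trained in common protocols, records are checked weekly and eligibility is reviewed jointly across sites, all of which make a large site difference less likely. An imbalance by site could be examined in the planned sensitivity analysis, and the interaction test would ordinarily be fitted with site in its model. All of this stands, and it limits the point to a minor one. It does not put site into the primary estimate, because a sensitivity analysis and an interaction test are separate from it.

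A reader might infer three stronger things that the article does not support:

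- **That allocation runs separately at each site.** Only the envelope seed is stated to be by site: 2 × 6 = 12 of 184 participants, or 6.5%. Separate minimisation within site is plausible but not stated. It therefore cannot be said that the model omits a factor known to have structured the whole allocation.
- **That the primary result is biased or its type I error inflated.** With arms balanced within site the test is conservative and the estimate unbiased. If balance is left to chance, a given trial may carry an uncorrected imbalance, but there is no systematic direction to it.
- **That the secondary outcome models share the omission.** The article does not specify those models, so nothing can be said about their covariates.

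**Conclusion.** The point holds as a minor one. The text fixes the primary model's covariates without site, and nothing else in the article adds a site main effect to the model that gives the primary estimate. Which of the two consequences applies depends on whether minimisation runs within site, which the article does not say. On either reading, adjusting for site would help a little and do no harm.

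The sizes rest on an assumed site difference, equal-sized sites and, for the shift in the estimate, an assumed 55/45 split. They also use the residual SD implied by the plan's own sample size calculation. Within the 0.4 to 0.6 point range, neither consequence threatens the trial's conclusions.

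**What to change.** Add site as a fixed effect to the primary mixed model, alongside gender, age, pain duration and pain intensity. Keep the site-by-group test as a separate supportive check, so that whether site enters the primary model does not depend on its result. A sentence stating whether minimisation runs within site or across both would settle which consequence is relevant.

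The cost is one degree of freedom. Site is already recorded, so no new data are needed, and the stated 80 per group, 92 per group and 184 in total do not change.
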